#### General Information and Abstract of Thesis

Title in English:

The effect of art therapy on anxiety and quality of life following pregnancy loss

Keywords:

art therapy, pregnancy loss, quality of life, anxiety, prenatal grief, PGS

#### **Summary of the necessity of conducting the thesis:**

Pregnancy, childbirth, and motherhood are among the most significant events in women's lives and represent the pinnacle of the divine art of creation. The pregnancy period and beyond are vital parts of a family's existence and hold a special place in the social life of a community; the physiological transition from pregnancy to motherhood entails significant physical and psychological changes in a woman. Any deviation from the natural course of these changes, both physically and mentally, can create problems for the mother and subsequently for the family. For example, failure to complete the pregnancy process, including miscarriage and stillbirth, can lead to feelings of loss and grief in women. Grieving fundamentally helps individuals cope with the impact of both major and minor losses in life. Failing to navigate the grieving process within its natural framework may

result in psychological and even physical issues in women, such as various mental disorders including depression, anxiety attacks, suicidal thoughts, sexual dysfunction, sleep disorders, decreased self-esteem, eating disorders, difficulties in communicating with others, and ultimately a change in the quality of life. One of the most effective ways to combat anxiety and depression is through non-pharmacological interventions. Studies have shown that educational and skill-based interventions are effective in reducing depression and can improve the quality of life for mothers. Recently, the use of complementary therapies for depression treatment has been under investigation. One of the newer and more effective complementary therapies is art therapy, the benefits of which in solving psychological problems have been confirmed. Given that the duty of fertility health service providers is to consider all aspects of fertility health, its process and function, it seems that grief and its consequences have not received enough attention in follow-up care, and these types of care are lacking in the assessment of health service needs both from the perspective of providers and patients. On the other hand, considering that the empowerment of women in self-care has been a focus in recent years in international documents, facilitating the psychological adaptation process for women is also one of the important goals of midwifery care. Healthcare professionals play a vital role in creating positive changes in parents and preparing them for pregnancy and healthy parenting in the future. Therefore, given the burden of grief after pregnancy loss, the possibility of its progression towards depression, the current interest in alternative and non-pharmacological therapies, and the limited studies in this area, the necessity of conducting such an important and practical investigation is undeniable.

### **Summary of Implementation Method and Analysis Approaches:**

This research is a parallel randomized intervention study examining the correlation between art therapy, quality of life, and anxiety in women following pregnancy loss in hospitals affiliated with Tehran University of Medical Sciences. The research environment includes hospitals affiliated with Tehran University of Medical Sciences. The research population includes all women who have experienced miscarriage and stillbirth. The research sample, approved by the statistician with a sample size of 60 participants from

the research population, will be divided into intervention and control groups using block randomization.

**Inclusion Criteria:** History of miscarriage or stillbirth within the past 6 weeks, at least basic literacy skills, willingness to participate in the study, and grief confirmation using the Perinatal Grief Scale before childbirth questionnaire.

**Exclusion Criteria:** Mental illnesses, severe psychological reactions requiring referral to psychiatry and essential interventions, current use of antidepressant medication, unwillingness to participate in the study, and absence from all art therapy sessions.

Data collection tools in this research include:

1. Demographic information questionnaire including: age, education level, number of pregnancies, number of childbirths, number of miscarriages.
2. Perinatal Grief Scale (PGS) consisting of 33 items and three subscales: active grief (11 questions), difficulty coping (11 questions), and despair (11 questions), designed to measure grief in the loss before childbirth (miscarriage, ectopic pregnancy, fetal death, and neonatal death). The questionnaire scoring is on a 5-point Likert scale with corresponding scores of 1, 2, 3, 4, and 5 for options "strongly disagree," "disagree," "neither agree nor disagree," "agree," and "strongly agree" respectively.
3. World Health Organization Quality of Life questionnaire, short version with 26 items designed to assess quality of life in four dimensions: health, psychological health, social relationships, and environmental health.
4. State-Trait Anxiety Inventory – A self-report psychometric scale measuring two distinct but related concepts of anxiety. Situational anxiety refers to consciously perceived emotional situations causing tension, fear, restlessness, worry, and increased nervous system activity. Personal trait anxiety is individual differences in the disposition to perceive or evaluate stressful situations as threatening or dangerous. Responses to these situations lead to increased anxiety (Lotfi Afshar, 1997).

Initially, women will complete the grief questionnaire, and if individual grief is confirmed, they will be included in the study. The intervention group will receive two sessions per

week, totaling four 90-minute art therapy sessions following a designed protocol. The participants will complete the anxiety, grief, and quality of life questionnaires are completed by participants at the beginning of the study. After 2 weeks of intervention and at the end of the intervention, the grief and anxiety questionnaires are completed again. Eight weeks after the intervention, all three questionnaires will be completed by participants. Upon entry into the study, participants will respond to the quality-of-life questionnaire. They will also respond to the quality-of-life questionnaire with a 4-week interval from the end of the intervention, both before and after the intervention, with a 2-week interval between assessments. The scores before and after the intervention will be compared using paired t-test.

No interventions will be made for the control group during the study period. However, after this time and for ethical considerations, if participants in the control group desire, a more condensed session (2 sessions) with the same content will be held for the control group.

Registration General, Specific, and Practical Objectives Main Objectives of the Plan:

- Determining the effect of art therapy on anxiety and quality of life following pregnancy loss in women attending hospitals affiliated with Tehran University of Medical Sciences in 2019.

Subsidiary Objectives of the Plan:

- Comparing the average grief score following pregnancy loss in the intervention and control groups at the beginning, after two intervention sessions, at the end of the intervention, and 8 weeks after the completion of the intervention in women attending hospitals affiliated with Tehran University of Medical Sciences in 2019.
- Comparing the average clear anxiety score following pregnancy loss in the intervention and control groups at the beginning, after two intervention sessions, at the end of the intervention, and 8 weeks after the completion of the intervention in women attending hospitals affiliated with Tehran University of Medical Sciences in 2019.

- Comparing the average hidden anxiety score following pregnancy loss in the intervention and control groups at the beginning, after two intervention sessions, at the end of the intervention, and 8 weeks after the completion of the intervention in women attending hospitals affiliated with Tehran University of Medical Sciences in 2019.
- Comparing the quality-of-life score following pregnancy loss in the intervention and control groups before and 8 weeks after the intervention in women attending hospitals affiliated with Tehran University of Medical Sciences in 2019.

Practical Objectives of the Plan: Considering that the responsibility of fertility healthcare providers is to pay attention to all aspects of fertility health, it seems that there has not been enough attention to grief issues and the consequences of this phenomenon in the follow-up services, as indicated by both healthcare providers and patients in healthcare service needs assessment. If the results of this study demonstrate the impact of art therapy on various aspects of grief, the improvement of the quality of life and anxiety of these women, it can be deemed cost-effective and free of any side effects. In addition, it can empower women in self-care, making it a beneficial method for controlling pre-birth grief.

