#### **Implementation Method:**

**Study Type:** The present study is a parallel randomized clinical trial involving 60 mothers (30 in the intervention group and 30 in the control group) who attend the hospitals of Tehran University of Medical Sciences following pregnancy loss. Individuals who meet the inclusion criteria, including a history of recent miscarriage or stillbirth within the last 6 weeks, having at least basic literacy skills, willingness to participate in the study, confirmation of grief using the PGS questionnaire, and residing in Tehran, will be enrolled in the study. At the beginning of the visit, the Perinatal Grief Scale (PGS) will be completed by the participants. Those scoring 92 or higher on the total grief score, or 34 or higher on the active grief or 30 or higher on the difficulty coping subscale, or 27 or higher on the despair subscale, indicating high levels of grief, will be included in the study.

**Randomization Method:** This will be carried out using a block randomization method. Four-person blocks are selected so that Group A will be the intervention group and Group B will be the control group. Each of the six possible scenarios will be written on separate cards, numbered from one to six. The numbers will then be written on paper, randomly selected, until the expected number of samples is complete. The concealment of the sequence will be done using sealed envelopes, each containing one of the designated letters in order, sealed, and given to the researcher. The randomization and concealment process will be performed by a statistical consultant.

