**Blinding Procedure:** Due to the nature of the intervention, blinding is not feasible. Subsequently, participants will be informed about the study and will complete an informed consent form. Demographic, grief, anxiety, and quality of life questionnaires will be completed by them. The selected samples will undergo four 90-minute sessions of art therapy and pottery weekly for two weeks according to the designed program detailed below, and anxiety and grief questionnaires will be completed after two sessions of art therapy and at the end of the intervention. Eight weeks after the intervention, the questionnaires will be completed again. During the intervention period, the control group will not receive any art therapy interventions, except for routine medical care following pregnancy loss. To ensure research ethics, all participants will be assured of the confidentiality of the research results. Additionally, after the intervention period, a condensed intervention (2 sessions) will be offered to the control group if the individuals are willing. To combat Miss to follow up issues, participants will be reminded of their class attendance one day before each art therapy session through SMS messages. The completion of questionnaires eight weeks after the intervention will be done electronically.

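### Absence from art therapy is listed as an exclusion criterion, which can remove women only after randomisation and only from the art arm

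*Protocol*

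**What the plan says.** Under Summary of Implementation Method and Analysis Approaches, the sample "will be divided into intervention and control groups using block randomization". Implementation Method gives the numbers as "60 mothers (30 in the intervention group and 30 in the control group".

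The exclusion criteria in the same summary begin with items that can be checked at screening, such as mental illness and current antidepressant use. They close with "unwillingness to participate in the study, and absence from all art therapy sessions".

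The summary gives sessions to the intervention group only, "totaling four 90-minute art therapy sessions following a designed protocol". For the controls, Implementation Method says that during the intervention period "the control group will not receive any art therapy interventions, except for routine medical care following pregnancy loss". Afterwards, "a condensed intervention (2 sessions) will be offered to the control group if the individuals are willing".

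Against loss to follow-up, Implementation Method (Blinding Procedure paragraph) says that "participants will be reminded of their class attendance one day before each art therapy session through SMS messages". It adds that the 8-week questionnaires are completed electronically and mentions no reminder for them.

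**The concern.** An exclusion criterion should be decidable before allocation and should apply alike to both arms. Attendance at sessions meets neither condition. A woman's attendance is unknown until she has been randomised to the art arm and the sessions have run, and a control woman has no session to miss.

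Randomisation makes the two sets of 30 women comparable. If some art-arm women are then removed because of how they behaved after allocation, while the control women who would have behaved the same way stay in, that comparability is lost. A difference between the remaining groups can then reflect who was removed as well as what art therapy did. If the excluded women's later questionnaires are not collected, no later analysis can recover them.

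Follow-up effort raises a second, lesser issue. A reminder about class attendance reaches only women who have classes. Control women get no described reminder for any assessment. Neither arm gets one for the 8-week questionnaires, which are the only post-baseline point at which the stated objectives compare quality of life.

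**Working it through.** **Step 1: when and to whom the criterion can apply.**

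| Criterion | Knowable before allocation? | Can apply to controls? |
|---|---|---|
| Mental illness, antidepressant use | Yes | Yes |
| Unwillingness to participate | Yes | Yes |
| Absence from sessions | No | No, as they have none in the study period |

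The two condensed sessions offered to controls do not change the last row, because they come afterwards and are optional. Implementation Method repeats the inclusion criteria but neither repeats nor corrects the attendance criterion. Nothing gives controls a matching rule, and nothing says that excluded women are still followed and analysed as allocated.

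**Step 2: size of the shift.** The protocol gives no attendance rate, dropout rate or SD, so there is no stated figure to reproduce. Let m be the mean of the attenders, k the number dropped out of 30, and D the amount in SD by which the dropped women would score worse.

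- Mean of all 30 as randomised: [(30 - k) x m + k x (m + D)] / 30 = m + (k/30) x D.
- Mean after dropping k women: m.
- Shift: (k/30) x D.

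| Reading of the phrase | k (assumed) | D = 0.3 | D = 0.8 |
|---|---|---|---|
| Attended none of four | 1 | 1/30 x 0.3 = 0.01 | 1/30 x 0.8 = 0.03 |
| Attended none of four | 2 | 2/30 x 0.3 = 0.02 | 2/30 x 0.8 = 0.05 |
| Missed at least one | 9 | 9/30 x 0.3 = 0.09 | 9/30 x 0.8 = 0.24 |

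If D is negative (the dropped women would have scored better), the shift has the same size and works against art therapy.

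**Step 3: scale.** Assume two-sided alpha 0.05 and 80% power; the protocol states neither. With 30 per arm the detectable difference is (1.96 + 0.84) x sqrt(2/30) = 0.72 SD by the normal approximation. The largest shift in the table is 0.24/0.72, a third of that. The literal-reading maximum is 0.05/0.72, about 7%.

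**Step 4: effect on the false-positive rate.** Take a between-arm comparison with no true effect and total SD 1. With p = k/30, the variance among attenders is v = 1 - p(1 - p)D², the standard error is SE = sqrt(v/(30 - k) + 1/30), and the two-sided type I error is P(|Z + shift/SE| > 1.96).

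- k = 2, D = 0.8: v = 0.960, SE = 0.260, shift/SE = 0.053/0.260 = 0.21, type I error 0.055.
- k = 9, D = 0.8: v = 0.866, SE = 0.273, shift/SE = 0.24/0.273 = 0.88, type I error 0.142.
- All 30 kept in each arm: shift 0, type I error 0.05.

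**Step 5: the reminder.** The effect of one-arm reminders cannot be given a size or a sign from the protocol. Reminders to attend lower non-attendance, so they reduce the number who meet the exclusion. If unreminded controls are lost and are the more distressed, the control mean looks better than it should, which works against art therapy. If the lost controls are those who feel recovered, the opposite holds.

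**The case against.** The strongest reply is that little may turn on this. Read literally, the phrase covers only women who attended no session at all. There may be none or very few, and the shift is then a few hundredths of an SD. The item appears once, in the summary. The protocol says excluded but does not say that questionnaires are discarded, and it defines no analysis population; an SAP that is not shown might keep these women. Most of this stands as a limit on size and on certainty. It does not rescue the criterion, because the protocol states the rule and nothing in it offsets the rule.

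A reader might infer three stronger points that the protocol does not support:

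- **That the bias certainly favours art therapy.** This needs non-attenders to be the more distressed. That is plausible in women enrolled for high grief scores, but non-attenders could equally be women who feel recovered.
- **That the one-arm SMS adds to a bias towards art therapy.** As shown in the working, it could run the other way. Electronic completion at 8 weeks is not confined to one arm, and the later offer of sessions may encourage controls to stay, so unequal follow-up is a possibility and no more.
- **That the criterion "severe psychological reactions requiring referral to psychiatry and essential interventions" is also a one-arm removal.** It stands beside ordinary screening criteria, and nothing says it is applied after entry or is detected mainly in the art arm.

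**Conclusion.** The point holds for the attendance criterion. As written, it is a post-randomisation exclusion that can operate in one arm only, and its wording leaves open which women it removes. Both readings share the structural error, whichever way the bias runs.

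The literal reading probably makes the effect small, and the larger shift of 0.24 SD needs both the wider reading and the top of the assumed range for D. The type I error figures rest on the same assumptions and on a between-arm comparison at two-sided 0.05. The uneven reminder is a secondary weakness with no quantifiable effect. The case for acting rests on the break in the randomised comparison and on how little it costs to avoid.

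**What to change.** 1. Delete absence from sessions from the exclusion criteria. Record the number of sessions attended as adherence and report it descriptively.
2. State that questionnaires continue to be collected from women who do not attend, subject to their right to withdraw.
3. State that every randomised woman is analysed in her allocated arm. Any attenders-only analysis is supportive.
4. Send the same questionnaire reminder to both arms before each post-baseline assessment, including the electronic one at 8 weeks. The class reminder can stay as part of delivering the intervention.

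The cost is a change of wording and a few SMS messages per woman. The estimate may be less favourable than one among attenders only. No change to psychiatric referral or to clinical withdrawal is proposed.

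### The only test the protocol names is a within-arm before-after paired t-test, which contradicts the randomised parallel design and the between-arm objectives

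*Protocol*

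**What the plan says.** Under Implementation Method, the study is a "parallel randomized clinical trial involving 60 mothers (30 in the intervention group and 30 in the control group"), allocated in blocks: "Four-person blocks are selected so that Group A will be the intervention group and Group B will be the control group".

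The main objective, in the Summary of Implementation Method and Analysis Approaches, is causal: "Determining the effect of art therapy on anxiety and quality of life following pregnancy loss". The subsidiary objectives in the same section are comparisons between arms:
- Grief: "Comparing the average grief score following pregnancy loss in the intervention and control groups", at four time points (start, after two sessions, end of intervention, 8 weeks later).
- Clear anxiety: "Comparing the average clear anxiety score following pregnancy loss in the intervention and control groups", at the same four time points. Hidden anxiety has the same wording.
- Quality of life: "Comparing the quality-of-life score following pregnancy loss in the intervention and control groups before and 8 weeks after the intervention".

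No test is attached to any of these objectives. The only test named in the protocol closes the description of the questionnaire schedule in that section, directly after two sentences about quality of life: "The scores before and after the intervention will be compared using paired t-test".

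Entry requires a loss within the past 6 weeks and a high Perinatal Grief Scale (PGS) score. "Those scoring 92 or higher on the total grief score" are included, as are women who reach the cut-off on any one of the three subscales.

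**The concern.** A paired t-test of before against after asks whether the mean score in one group of women changed. It does not ask whether the change differed between women given art therapy and women not given it, which is what the objectives ask. It also uses two time points, while the grief and anxiety objectives use four.

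The mismatch matters more than usual in this population. The women have had a recent loss and are chosen because their grief is high. The protocol's own Introduction describes grief as a natural course ending in resolution. Scores are therefore likely to improve in both arms over a follow-up that runs to 8 weeks after the intervention. The control arm is there to remove that improvement from the estimate, and the named test does not use it.

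This is not a complaint that detail is missing. The protocol states a test, and the test does not fit the question. A statistical analysis plan with a between-arm model would have to overrule the sentence.

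**Working it through.** The protocol gives no figure of its own to reproduce here: it states no significance level, SD, correlation or expected change. From the document come 30 women per arm, the paired t-test, entry by high PGS within 6 weeks, and follow-up at 8 weeks. Everything else below is an assumption shown as a range: two-sided 5% level, no dropout, equal SDs before and after, and a true art-therapy effect of zero.

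**1. Paired test in one arm when everyone improves naturally.** Let the natural improvement be d (in SD units) and the before-after correlation r. The SD of the change is √(2(1−r)), so the noncentrality parameter is d·√30 / √(2(1−r)) with 29 degrees of freedom. For example:
- d = 0.3, r = 0.3: 0.3 × 5.477 / 1.183 = 1.39
- d = 0.5, r = 0.7: 0.5 × 5.477 / 0.775 = 3.54

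Probability of p < 0.05, although art therapy does nothing:

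| Natural improvement | r = 0.3 | r = 0.5 | r = 0.7 |
|---|---|---|---|
| 0 | 5% | 5% | 5% |
| 0.3 SD | 26.9% | 35.5% | 53.6% |
| 0.5 SD | 60.9% | 75.4% | 92.7% |

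**2. Between-arm comparison.** A natural change common to both arms cancels in the difference, so a test of arm keeps its level. In simulation (4,000 trials in each of 12 settings, baseline selected above a cut-off, correlation 0.6 or 0.8, natural recovery 0 or 0.3 SD), an ANCOVA of follow-up on arm and baseline was significant in 4.6% to 5.2% of trials.

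**3. One paired test per arm, with the p-values contrasted.** If each arm is significant with probability π and the arms are independent, the pattern of art therapy significant and control not significant occurs with probability π(1−π). Applied to the table:
- 0.3 SD: 0.269 × 0.731 = 19.7%; 0.355 × 0.645 = 22.9%; 0.536 × 0.464 = 24.9%
- 0.5 SD: 0.609 × 0.391 = 23.8%; 0.754 × 0.246 = 18.5%; 0.927 × 0.073 = 6.8%

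A between-arm test at this level would favour art therapy wrongly in 2.5% of trials. The maximum of π(1−π) is 25%, at π = 0.5. When π is near 1 the product is small, because control is then significant as well; the rule would then also miss a real effect.

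**4. Regression to the mean, for grief.** This applies only if the screening PGS also serves as the baseline. Simplify entry to one normal score above a cut-off c. The expected fall is (1−ρ)·φ(c)/(1−Φ(c)), with ρ the test-retest correlation. At the median (c = 0), φ/(1−Φ) = 0.399/0.5 = 0.798, so the fall is 0.4 × 0.798 = 0.32 SD (ρ = 0.6) or 0.2 × 0.798 = 0.16 SD (ρ = 0.8). For cut-offs from −0.5 to +0.5 population SD the simulated fall is 0.10 to 0.46 SD, and the paired test is significant in 14% to 83% of trials with no natural recovery at all.

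**The case against.** **The objectives do compare the arms.** This is correct. A reader might infer that the trial never compares its randomised groups, but the subsidiary objectives commit to doing so. What stands is a contradiction between those objectives and the one test named.

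**The sentence may concern quality of life only.** Its position supports that reading. The protocol would then name no test for grief or anxiety, and that silence may properly be left to the analysis plan. A reader might infer that every outcome would be analysed wrongly, but the text does not establish this. Quality of life is nevertheless part of the main objective, and on either reading the named test cannot answer the quality-of-life objective.

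**The regression-to-the-mean figures may not apply.** The protocol can be read as giving the PGS once for screening and again with the baseline questionnaires. If these are separate measurements, much of the regression occurs before baseline. Entry is also by total score or any subscale, not one cut-off, and nothing in the document places a cut-off at the population median. Step 4 is therefore conditional and the conclusion does not depend on it. Selection on the PGS reaches anxiety and quality of life only through their correlation with grief.

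**The protocol does not propose contrasting p-values between arms.** True. Step 3 only shows that the obvious way of bringing in the control arm with paired tests would not cure the problem. Its 25% is a maximum and cannot occur together with settings where the paired test is almost always significant.

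**Conclusion.** Wrong as written, and it should be corrected before analysis. The named test is within-arm, while the design and objectives are between-arm. This holds for quality of life on any reading, and for grief and anxiety if the sentence is meant to cover them.

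The direction of the error follows from the design: improvement that would have happened anyway is credited to art therapy. Its size depends on assumptions the document does not supply. With no true effect and natural improvement of 0.3 to 0.5 SD at correlations of 0.3 to 0.7, a false finding of change arises in about 27% to 93% of trials, against about 5% for a between-arm ANCOVA. Regression to the mean would add to this for grief to the extent that the screening score is also the baseline. A wrong conclusion is thus a substantial risk, not a certainty.

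**What to change.** Replace the paired t-test sentence with wording such as:

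*The arms are compared as randomised. Quality of life at 8 weeks after the intervention is analysed by ANCOVA on arm and baseline score. Grief and anxiety are analysed by ANCOVA, or by a repeated-measures mixed model with arm, visit, arm-by-visit and baseline score. Results are adjusted between-arm differences with 95% CI. Before-after changes within an arm are descriptive only.*

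The 8-week visit is the one in the quality-of-life objective. The sentences just before the paired t-test also mention a 4-week interval for this questionnaire, and the two should be reconciled. The wording should also name the visit that carries the result for grief and for anxiety, and say whether the screening PGS is the baseline value. The choice between ANCOVA and a mixed model is open; the comparison of arms is what cures the defect.

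The cost is one paragraph of protocol text. Baseline questionnaires are already completed by participants, so no new data are needed.

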### **Session Plan for Art Therapy Intervention:**

First Session: Warm-up Exercise: Introduction to Colors Main Exercise: Paper Collage or Images – Creating a Family Tree, Depicting Current State Relaxation Exercise: Listening to Instrumental Music and Relaxation Purpose: Familiarity with group members, Self-expression Duration: 90 minutes

Second Session: Warm-up Exercise: Color Spots Main Exercise: Full-length Image, Painting Worst Fears & Threatening Situations, Stress Ballooning Relaxation Exercise: Closing Eyes and Imagining a Calming Place Purpose: Expressing Anger, Fear, Stress Duration: 90 minutes

Third Session: Warm-up Exercise: Contrasting Colors, Lines, and Shapes Main Exercise: Pockets and Boxes – Self-portrait, Symbolic Representation of Talents or Abilities, Drawing a Support Circle and Peaceful Painting Relaxation Exercise: Looking in the Mirror and Showing Self-compassion Purpose: Self-worth, Abilities, Support Duration: 90 minutes

Fourth Session: Warm-up Exercise: Creating Personal Symbol with Clay Main Exercise: Making Seasons with Clay, Creating a Nest Tree and Bird and Storm-affected Tree, Writing a Letter to God and a Letter to Spouse Relaxation Exercise: Breathing and Music, Gratitude Purpose: Insight, Solutions, Hope and Future Duration: 90 minutes

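### The protocol lets benefit on grief, quality of life and anxiety stand as proof that art therapy is cost-effective and free of side effects, with no cost or separate adverse-event data planned

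*Protocol*

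**What the plan says.** The sentence at issue stands in the protocol under Practical Objectives of the Plan, within the Summary of Implementation Method and Analysis Approaches. Its condition, which also takes in anxiety, begins "If the results of this study demonstrate the impact of art therapy on various aspects of grief, the improvement of the quality of life and". Its conclusion is that "it can be deemed cost-effective and free of any side effects".

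The main objective in the same section is "Determining the effect of art therapy on anxiety and quality of life following pregnancy loss". The subsidiary objectives compare grief, the two anxiety scores and quality of life between the groups; for grief and anxiety they specify average scores.

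Four data collection tools are listed:
- for background, a "Demographic information questionnaire including: age, education level, number of pregnancies, number of childbirths, number of miscarriages";
- for grief, the "Perinatal Grief Scale (PGS) consisting of 33 items and three subscales";
- for quality of life, the "World Health Organization Quality of Life questionnaire, short version with 26 items";
- for anxiety, the State-Trait Anxiety Inventory (STAI).

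The exclusion criteria include "severe psychological reactions requiring referral to psychiatry and essential interventions". The second session in the Session Plan includes "Painting Worst Fears & Threatening Situations".

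**The concern.** The conclusion concerns cost and harm, but its only condition is benefit on efficacy scores. A treatment can lower mean anxiety and still harm some of the women who receive it, and it can work without being worth its cost. If the authors apply their own sentence to a positive result, they will assert safety and cost-effectiveness with nothing collected to support either.

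The question of harm is not idle here. The women are enrolled within six weeks of a loss because they score high on grief, and one exercise asks them to depict what they fear most. The one serious reaction that the protocol names appears only as an exclusion, and the protocol does not say when that exclusion operates.

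**Working it through.** The protocol gives no figure for this claim, so there is nothing to reproduce. The check compares the claim with the planned data, and a short calculation then shows what 30 women could support.

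**Step 1. Cost.** Cost-effectiveness needs at least costs or resource use by arm. The demographic form covers age, education and obstetric history. The other three tools are scales for grief, quality of life and anxiety. The objectives and the Implementation Method add no cost variable and no economic comparison. The quality-of-life scale could describe an effect, but no cost is set against it.

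**Step 2. Harm.** No tool is an adverse-event record, and neither the objectives nor the procedures mention one. Grief and anxiety are measured at baseline, after two sessions, at the end of the intervention and eight weeks later. The subsidiary objectives use them as averages in each group, and the summary adds paired t-tests of scores before and after. These are comparisons of means. A mean can fall while some women get worse.

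**Step 3. The exclusion.** The severe-reaction item shares a list with mental illness and current antidepressant use, which read as entry screens. The same list includes absence from all art therapy sessions, which can occur only after allocation. The list therefore mixes the two kinds, and the timing of the severe-reaction item is open.
- If it applies at entry only, the sample is selected for lower risk and any safety inference is limited to such women.
- If it also applies after allocation, women who reacted badly could leave the data.

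Neither reading supports a claim of no side effects at all.

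**Step 4. Illustration.** The Implementation Method gives n = 30 in the intervention group. Suppose, contrary to the plan, that harms were fully recorded and none occurred.
- One-sided exact 95% upper limit: 1 − 0.05^(1/30) = 0.095, or 9.5%.
- Two-sided exact 95% upper limit: 1 − 0.025^(1/30) = 0.116, or 11.6%.

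The chance of seeing no event in 30 women is (1 − p)^30. The true rates p below are assumptions, since the protocol gives none.

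| Assumed true rate | Chance of no event in 30 |
|---|---|
| 1% | 0.99^30 = 74% |
| 3% | 0.97^30 = 40% |
| 5% | 0.95^30 = 21% |
| 10% | 0.90^30 = 4% |

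Even a clean record in this arm would be compatible with a harm rate of several per cent.

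**The case against.** The strongest reply is that the sentence decides nothing in the trial. It stands in a paragraph on hoped-for usefulness, it is conditional and says only that the method can be so regarded, and no endpoint, test or sample size depends on it. It may be a loosely translated remark that a non-drug method is cheap and gentle. The first part of this stands: the point is an overclaim joined to a gap in data collection, and not an error in the analysis. The second part cannot be shown from the text, and the sentence as written makes both properties follow from benefit.

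A reader might also infer that the trial measures no harm of any kind. That goes too far. Heightened anxiety and grief are what the STAI and the Perinatal Grief Scale register, and both are repeated after the second session, so the worst-fears exercise is followed by a measurement. What is missing is separate recording of events in individual women.

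A reader might further infer that harmed women will be lost from the data, or that the trial is bound to publish a safety claim. The protocol establishes neither. The exclusion may be an entry screen only, and no passage plans such a report. Nor does anything in the protocol show that the exercises cause harm.

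Finally, tabulation of adverse events is often left to a statistical analysis plan. That is fair for the tabulation, but no analysis plan can supply data that were not collected or make this inference valid.

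**Conclusion.** The point holds in this form: the protocol attaches two conclusions to a positive efficacy result, and the planned data can support neither. For cost, no variable is described. For harm, there are group averages on two scales, no separate event recording, and an exclusion of unstated timing that weakens a safety inference on either reading.

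The efficacy comparisons are untouched. The calculation assumes 30 exposed women with complete harm data and no events, and the true rates are assumed, so it shows the limit of what this arm could ever support and does not estimate risk. The point rests on the protocol alone, as the analysis plan is not shown.

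**What to change.** 1. Delete the clause claiming cost-effectiveness and freedom from side effects.
2. State that the severe-reaction exclusion is used for eligibility only and does not remove any randomised woman from the analysis. This concerns who is counted and leaves clinical handling to those responsible for it.
3. Add a short harm item to the existing post-baseline questionnaires in both arms, asking about psychiatric referral and any new psychological or antidepressant treatment.
4. Record the reason for any withdrawal when it happens. A questionnaire item alone would miss women who leave in distress and complete nothing further.
5. Report counts by arm among all randomised women, with the number whose harm data are missing, and limit any safety statement to those counts and their exact intervals.

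The cost is slight extra recording and a less favourable claim. With 30 women per arm the intervals will be wide, so the counts can describe what was seen but cannot establish safety.
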